#### 5.2.3. Screening and final enrollment into the study.

Interested participants will undergo screening based on established inclusion/exclusion criteria and mental health assessments. The screening process helps identify those needing immediate mental health referrals and confirms program suitability. Eligible families who wish to participate will complete the informed consent process, with written consent obtained from caregivers and written assent from adolescents, ensuring full understanding of the program and voluntary participation.

#### 5.2.4. Randomization and allocation.

The study will employ a cluster-randomized controlled trial design, where participating clinics, rather than individual participants, will be randomized to intervention or control groups. This approach minimizes contamination between groups and strengthens study validity [48]. Clinic allocation will be determined using a computer-generated randomization sequence to ensure unbiased assignment and concealment [49] (see Fig 2).

**Fig 2 pone.0325854.g002:**
[figure not shown]
Randomization process and group allocation.

#### 5.2.6. Intervention group and description of the intervention conditions.

The clinics allocated to the intervention group will receive the Multiple-Family Group Therapy (MFGT) intervention in addition to the usual care. All eligible and consenting adolescents living with HIV/AIDS and their families who are associated with this clinic will be assigned to the MFGT intervention condition. The MFGT intervention will involve a series of structured group sessions facilitated by parent peers and community health workers trained by the research team. ALHIV and their families will be invited to participate in 16 program sessions, each lasting 90 minutes, and will be held on clinic days over 14 weeks. The MFGT will combine group discussions and activities fostering support, learning and interaction both within the family and among families.

Sessions on the MFGT will begin with introducing participants to one another, the facilitators, and the program curriculum. This initial session is designed to help participants start building connections and becoming familiar with each other. It will also establish the foundation for future sessions by setting group ground rules and determining the meeting location and schedule. Subsequent sessions will concentrate on areas such as respectful communication, support and resilience building, problem-solving, conflict resolution, stress management, and enhancing family relationships and practices. Additionally, to tackle stigma stemming from societal myths about HIV/AIDS, a session may be included to provide adolescents and their families with behavioral health knowledge, fostering discussions about stereotypes, stigma, and their effects on mental health and adherence to ART.

#### 5.2.7. Control group and description of the control conditions.

The clinic allocated to the control group will continue to provide standard HIV care and treatment services. All eligible and consenting adolescents living with HIV/AIDS and their families who are associated with the control clinic will be assigned to the “treatment as usual” condition which includes adherence support from community adolescent treatment supporters, adherence counselling from health workers, Nutritional counselling, health education, treatment of opportunistic infections, medical care and mobile reminders of schedule hospital appointment and treatment adherence. Other services will include defaulter tracing and loss to follow-up services. This control group will allow the research team to compare the outcomes of the adolescents and families receiving the MFGT intervention to those who continue to receive the standard HIV care, thereby evaluating the effectiveness of the MFGT program.

#### 5.2.8. Criteria for discontinuing or modifying allocated interventions.

Participants in the intervention group (MFGT plus usual care) may discontinue the program for several reasons, including voluntary withdrawal at any time without penalty, medical reasons if participation causes significant distress or interferes with treatment, safety concerns if participation poses risks to the participant or others, or extended absence such as missing three consecutive sessions without communication. The intervention may be modified through alternative scheduling or individual make-up sessions for those unable to attend regular meetings, additional support or modified activities for participants experiencing specific challenges, or adjustments to group dynamics and composition while maintaining core intervention components. All discontinuations and modifications will be documented and reported in the study findings, and participants who discontinue MFGT will continue to receive usual care through their clinic.

### 5.3. Evaluation phase

The final phase of the study is the evaluation phase, which focuses on assessing the effectiveness of the culturally-adapted MFGT intervention. The evaluation phase of the study will be iterative and formative in nature [51]. Attention will be paid to both the effectiveness of the MFG intervention and the participants’ experiences throughout the program [52]. The evaluation will be achieved in three steps:

#### 5.3.1. Step 1: Process evaluation.

The process evaluation aims to assess the MFGT intervention’s implementation and identify potential improvements [53,54]. This evaluation will be conducted through session observations, facilitator and participant interviews, and review of attendance records, with findings used to optimize the program for the Ghanaian context.

The evaluation will focus on four key aspects: reach (examining enrollment, attendance, and retention rates), quality (assessing program materials and delivery components), implementation fidelity (monitoring adherence to planned activities), and participant satisfaction (gathering feedback through surveys, interviews, and focus groups). This comprehensive evaluation approach ensures that all aspects of program delivery are examined while identifying areas for refinement and improvement.

#### 5.3.2. Step 2: Impact evaluation.

The impact evaluation will assess the MFGT intervention’s immediate effectiveness through the use of standardized questionnaires. This phase will assess the immediate changes in the targeted outcomes (depression, anxiety, and ART adherence). This comprehensive evaluation approach will help determine whether the intervention has achieved its intended objectives and produced meaningful changes in participants’ mental health and treatment outcomes.

#### 5.3.3. Step 3: Outcome evaluation.

The final evaluation phase will assess the MFGT intervention’s long-term effects. Long-term effects will be measured at 3 and 6 months post-intervention, focusing on sustained improvements in mental health outcomes and ART adherence. This longitudinal assessment will help determine the program’s lasting impact on participants’ health status and quality of life [54].

#### 5.3.4. Study hypothesis.

We hypothesize that;

ALHIV in the intervention arm (MFGT group) would have a significant reduction in depression and anxiety and improved adherence to ART, compared to ALHIV in the control condition.Two variables- family functioning and HIV-related stigma will mediate the effects of the MFGT intervention on the primary outcomes (Depression and Anxiety) and the secondary outcome (Antiretroviral therapy (ART) adherence).

#### 5.3.5. Primary outcome measures.

The study’s primary outcome is the improvement in mental health and overall well-being of adolescents living with HIV/AIDS, specifically focusing on changes in depression and anxiety symptoms. Depression will be measured using the Patient Health Questionnaire (PHQ-9), a validated 9-item self-report tool that evaluates symptom presence and severity [55]. The PHQ-9, validated for use with Ghanaian adolescents [56], uses a 4-point scale (0–3) with total scores ranging from 0–27, categorizing depression as moderately severe (10–14), severe (15–19), or very severe (20–27).

Anxiety will be assessed using the Generalized Anxiety Disorder (GAD-7) scale, a 7-item self-report measure also validated for Ghanaian adolescents. The GAD-7 uses a similar 4-point scale with total scores ranging from 0–21, categorizing anxiety as moderate (10–14) or severe (15–21). A cutoff score of ≥10 indicates moderate to severe anxiety symptoms, providing a clear metric for evaluating the MFGT intervention’s impact on participants’ mental health [57,58].

#### 5.3.6. Secondary outcome measure.

Adherence to antiretroviral therapy will be measured as a secondary outcome using the validated Three-Item Self-Report Measure for Medication Adherence [59]. This tool assesses medication adherence through three questions: the percentage of HIV medication taken in the last 4 weeks (0–100% scale), the number of days missed taking medication in the last 4 weeks, and a self-evaluation of adherence quality (5-point Likert scale from “very poor” to “excellent”). These combined measures provide a comprehensive assessment of ART adherence, helping establish the relationship between mental health outcomes and HIV treatment compliance, thus supporting the rationale for implementing the MFGT intervention.

#### 5.3.7. Mediators.

In addition to the primary and secondary outcome variables, the study will also examine potential mediating factors (Family functioning, HIV-related stigma) that may influence the relationship between the MFG intervention and the desired outcomes.

Family functioning will be measured using the McMaster Family Assessment Device (FAD), a 60-item self-report instrument evaluating six domains: problem-solving, communication, roles, affective responsiveness, affective involvement, and behavior control [60]. The FAD has been validated across multiple African contexts, including South Africa, Ethiopia, and Uganda, making it suitable for assessing family dynamics before, during, and after the MFGT intervention [61–63].

HIV-related stigma will be assessed using the Berger HIV Stigma Scale, which measures enacted, internalized, anticipated, and vicarious stigma [64]. The Berger HIV Stigma Scale (HSS) is a widely used measure of HIV-related stigma, demonstrating good reliability and validity across diverse populations [65] and the African context [66]. The scale has been recently validated in Ghana, resulting in a 34-item version with high reliability (α = 0.808) and maintaining the original scale’s four-factor structure [67]. This validated tool will provide a culturally appropriate measure of HIV-related stigma among adolescent participants in Ghana.

#### 5.3.8. Data collection.

The data collection process for this study will be executed in three distinct phases.

##### 5.3.8.1. *Adaptation phase.*

The adaptation phase will utilize focus group discussions (FGDs) and in-depth interviews to gather qualitative data essential for adapting the MFGT intervention to the Ghanaian context. FGDs will be conducted with groups of 6–8 participants, including ALHIV, their caregivers, and healthcare providers. Additionally, in-depth interviews will be held with 10 key stakeholders, including policymakers, community leaders, and experts in HIV/AIDS and adolescent mental health, to understand broader contextual factors and potential implementation challenges.

##### 5.3.8.2. *Pilot implementation phase.*

We will gather qualitative data through focus group discussions and in-depth interviews to gain deeper insights into feasibility, acceptability, and perceived effectiveness of the adapted MFGT program. The FGDs will explore the participants’ experiences, perceptions, and feedback on the adapted MFG intervention.

##### 5.3.8.3. Evaluation phase.

The evaluation will include quantitative assessments of primary outcomes (using PHQ-9 and GAD-7 scales), secondary outcomes (ART adherence using Wilson’s 3-item scale), and mediating factors (McMaster Family Assessment Device and Berger HIV stigma scale) at multiple time points: baseline, post-intervention, 3-month follow-up, and 6-month follow-up. Qualitative data will be gathered through focus group discussions with adolescents, caregivers, and program facilitators to understand the intervention’s long-term impact and sustainability.

#### 5.3.9. Data management and analysis plans for quantitative and qualitative data.

The data entry will be conducted by an independent staff member not involved in the research team, who will input data into separate datasheets. This ensures that researchers can conduct analyses while remaining blinded to group allocation. The quantitative analysis will involve descriptive statistics at all time points, with repeated-measures ANOVA examining changes in primary and secondary outcomes across baseline, post-intervention, and follow-up periods. Exploratory subgroup analyses using independent t-tests will investigate differential intervention effects based on factors like age, gender, and socioeconomic status. For mediating factors (family functioning and HIV-related stigma), correlation analyses and structural equation modeling will examine relationships with primary and secondary outcomes, with appropriate techniques employed to handle missing data.

The qualitative data analysis will utilize specialized software (NVivo) for coding and organization, following Clarke and Braun [68] thematic analysis approach. This involves data familiarization, initial coding, theme development, review, and refinement. The analysis process will include multiple researchers to ensure reliability, with peer debriefing sessions and member checking to validate findings’ accuracy and trustworthiness.

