**Methods:**

A total of 80 ALHIV (aged 10–19 years at enrollment) will be recruited from two HIV clinics and each clinic will be randomized to one of two study conditions (MFGT group and control group). The study will be conducted in three phases: 1) Adaptation Phase – Qualitative data collection through focus group discussions and in-depth interviews with key stakeholders (adolescents, caregivers, community leaders and healthcare providers) to inform the adaptation of the MFGT intervention for the Ghanaian context; 2) Pilot Implementation Phase – Quantitative assessments (PHQ-9, GAD-7, Wilson’s 3-item adherence scale, FAD, Berger HIV Stigma Scale) and qualitative data collection (focus groups, interviews) to evaluate the feasibility, acceptability, and preliminary effectiveness of the adapted MFGT intervention; and 3) Evaluation Phase – Continuation of the quantitative and qualitative data collection, as well as a cost-effectiveness analysis, to assess the long-term impact, sustainability, and scalability of the MFGT intervention.

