## 1. Introduction

Globally, 38.4 million people are living with HIV, of which 1.7 million are children aged 0–14 years [1]. Sub-Saharan Africa contributes substantially to the HIV burden, reflected in the high HIV prevalence, mortality and morbidity [2]. Relating to Ghana, about 1.7% of population is living with HIV, with adolescents aged 15–19 years contributing to 0.7% of the HIV burden [3]. The diagnosis of HIV potentiates a cascade of mental health problems that impact all aspect of HIV prevention, treatment/management. This vulnerability is significantly elevated in adolescents who have heightened risk for mental health problems owing to their developmental stage [4]. In a recent global meta-analytic study, the prevalence of depression among ALHIV was 26.07%, with females (32.15%) and older adolescents aged 15–19 years (37.09%) recording the highest rate than males (25.07%) and younger adolescents aged 10–14 years (29.82%), respectively [5].

Focusing on SSA, a recent systematic review found that 25% of ALHIV screened positive for any psychiatric disorder, whereas 30–50% presented with emotional, behavioral difficulties or significant psychological distress [6]. Despite the paucity of epidemiological studies in Ghana, existing evidence suggests that ALHIV suffer from discrimination and rejection, ushering them into profound psychological distress such as suicidal thoughts and hopelessness [7] that often culminate into poorer psychosocial adjustment [8]. Unaddressed mental health problems in ALHIV contribute to not only mental health burden but also negatively impact on treatment adherence, prevention of HIV through the adoption of safe sexual practices and behaviors, school attendance and academic achievement [9].

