#### 4.3.1. Inclusion criteria.

Adolescents aged 10–19 years (as per WHO definition of adolescence) with confirmed HIV-positive status, aware of their HIV status and currently receiving antiretroviral therapy (ART). Primary caregiver of an eligible adolescent participant aged 18 years or older and aware of the adolescent’s HIV status. Additional criteria include adolescents and their caregivers residing in Lower Manya Krobo district, able to communicate in either English or the local language and willing to participate in group sessions.

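### With one clinic per arm, age and gender should be prespecified as covariates, with time interactions, in the main outcome model; at present their only stated role is in exploratory subgroup tests

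*Protocol article*

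**What the plan says.** **Allocation.** The abstract's Methods state that participants are "recruited from two HIV clinics and each clinic will be randomized to one of two study conditions". Section 5.2.4 confirms that "participating clinics, rather than individual participants, will be randomized to intervention or control groups". No matching or stratification on age or gender is described. Section 5.2.6 gives the intervention to "All eligible and consenting adolescents living with HIV/AIDS and their families who are associated with this clinic", and section 5.2.7 does the same for the control clinic. Section 4.3.1 admits the full range of adolescence, 10 to 19 years.

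**Prognosis.** The Introduction cites a global meta-analysis of depression in adolescents living with HIV, "with females (32.15%) and older adolescents aged 15–19 years (37.09%) recording the highest rate than males (25.07%) and younger adolescents aged 10–14 years (29.82" (per cent). Depression, measured by PHQ-9, is a primary outcome (section 5.3.5).

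**Analysis.** Section 5.3.9 names "repeated-measures ANOVA examining changes in primary and secondary outcomes across baseline, post-intervention, and follow-up periods". It lists no covariates, and does not say that the model is unadjusted. The only role it gives to "factors like age, gender, and socioeconomic status" is in exploratory subgroup comparisons, made with independent t-tests, of whether the intervention effect differs.

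**The concern.** Randomising individuals would balance age and gender on average and within calculable limits. Randomising two clinics cannot be relied on to do so: whatever difference exists between the two caseloads becomes a difference between the arms. The protocol itself reports that both factors are related to a primary outcome.

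The role it gives them does not deal with this. A subgroup test asks whether the MFGT effect differs between girls and boys, or between younger and older adolescents. It does not correct the overall comparison when one clinic has more girls or more 15- to 19-year-olds. Part of a known, measured case-mix difference could then be read as an MFGT effect, or could hide one.

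**Working it through.** **Yardstick.** Section 5.2.5 plans for a standardised effect of 0.6 with 36 per arm (72 in total). A one-sided 5% two-sample t-test with 80% power needs 35.04 per arm, which rounds up to 36 and reproduces the 72. The 0.6 is used below only as a scale.

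**Step 1: size of the age and gender effects.** The Introduction's prevalences are converted to shifts on a latent normal scale, z being the standard normal quantile:
- Gender: z(0.3215) − z(0.2507) = −0.464 + 0.672 = 0.209 SD
- Age band: z(0.3709) − z(0.2982) = −0.329 + 0.530 = 0.200 SD
- Sum, assuming the two add: 0.409 SD

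**Step 2: comparison of follow-up scores, unadjusted.** Bias = imbalance × 0.409. The documents do not give the mix of either clinic, so the imbalance is an assumption, taken as equal on both factors and in the same direction.

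| Imbalance (points) | Bias (SD) | Share of 0.6 | Rejection with no MFGT effect, nominal two-sided 5%, 36 per arm |
|---|---|---|---|
| 20 | 0.2 × 0.409 = 0.082 | 14% | 6.4% |
| 30 | 0.3 × 0.409 = 0.123 | 20% | 8.1% |

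Rejection rates come from the noncentral t distribution with noncentrality bias × √(36/2).

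If the test used the group main effect averaged over the four visits, nothing would cancel either. With an assumed within-person correlation of 0.5, the SD of a four-visit mean is √(0.5 + 0.5/4) = 0.791. The standardised bias is then 0.082/0.791 = 0.10 or 0.123/0.791 = 0.16, with rejection of 7.2% or 10.0%.

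**Step 3: change from baseline (group-by-time contrast).** If the age and gender effects are multiplied by (1 + g) after baseline, the bias in change is imbalance × 0.409 × g. A constant effect (g = 0) cancels. The table is for a 30-point imbalance; the simulation used 40 per arm, no true effect and correlation 0.5.

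| Growth g | Bias by formula (SD) | Bias simulated (SD) | Simulated, age and gender adjusted (SD) |
|---|---|---|---|
| 0 | 0 | 0.004 | 0.001 |
| 50% | 0.061 | 0.059 | −0.004 |
| 100% | 0.123 | 0.123 | −0.002 |

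**Step 4: baseline score as the only covariate.** With correlation 0.5, the bias is 0.123 × (1 + g − 0.5). That is about 0.06 SD at g = 0 and 0.12 SD at g = 50%. The baseline score alone therefore does not replace age and gender.

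**Step 5: price of adjustment.** With 40 per arm and correlation 0.5, the variance of an individual change is 2 × (1 − 0.5) = 1, so the unadjusted standard error is √(2/40) = 0.22 SD. At a 30-point imbalance on both factors, arm correlates 0.3 with each, and the two factors correlate 0.09 with each other. The R² of arm on both is 2 × 0.09/1.09 = 0.165, which multiplies the standard error by 1/√(1 − 0.165) = 1.09. The result is about 0.245, and about 0.25 in simulation.

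**The case against.** **Silence is not exclusion.** A condensed article may leave the covariate list to a fuller plan. A reader might infer that the plan rejects adjustment; it does not, and that lowers confidence. But the section names a model and assigns age and gender a specific role, one that does not address imbalance. The point is an improvement to a stated method.

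**The named analysis looks at change.** A reader might infer that any age or gender difference between the clinics passes in full into the estimated MFGT effect. The documents do not support that. Section 5.3.9 describes changes across visits that include baseline, and in that contrast a constant effect cancels. The Introduction reports prevalences and does not show that age or gender predicts change. This objection stands, and it limits the bias in that contrast to differences in course. What remains open is that the section does not say which ANOVA term tests MFGT.

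**The inputs are weak.** The prevalences are pooled worldwide, and the overall figure (26.07%) lies below both age-band figures, so they cannot all describe one sample. They concern depression only; no age or gender difference is given for anxiety or adherence. Adding the two effects is an assumption, as is the imbalance. The sizes are therefore illustrative.

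**The larger problem is untouched.** With one clinic per arm, arm and clinic are inseparable. At assumed intraclass correlations (ICC) of 0.01 to 0.05, the clinic difference alone has an SD of √(2 × ICC) = 0.14 to 0.32, which exceeds the bias discussed here. This is correct. It is a reason not to oversell adjustment, but no reason to leave a measured component in.

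**Conclusion.** The point holds in a limited form. Clinic-level allocation of two units does not balance age or gender, the protocol links both to depression, and the only use it states for them does not protect the main comparison.

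The size is modest and conditional. It is about 0.08 to 0.12 SD for an unadjusted comparison of follow-up scores at an assumed 20- to 30-point imbalance on both factors. In the change contrast it is zero for constant effects; at 30 points it is about 0.06 SD if they grow by 50% and 0.12 SD if they double. The actual imbalance, the within-person correlation and any growth of the effects are not in the documents.

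A reader might also infer that adjustment would make the two-clinic comparison sound. It would not: it removes only the part due to these two measured factors.

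**What to change.** In section 5.3.9:

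1. Prespecify age (continuous, in years) and gender as covariates, **with their interactions with time**, in the repeated-measures model for PHQ-9, GAD-7 and ART adherence. Main effects alone shift all visits equally and leave the group-by-time contrast unchanged. An alternative is an ANCOVA of follow-up scores with age, gender and the baseline score as covariates.
2. State which model term tests the MFGT effect.
3. Report the unadjusted result as a sensitivity analysis.
4. State that adjustment does not remove the complete confounding of arm with clinic.

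**Cost.** A few sentences, and no new data, since the subgroup analyses already require both variables. The model uses a few more degrees of freedom. If the clinics differ strongly on these factors, the standard error rises somewhat: about 0.25 against 0.22 SD in the change contrast at a 30-point imbalance. The choice should be fixed before outcome data are seen.
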